## Abstract

Hyperlactatemia occurs frequently after brain tumor surgery. Existing studies are scarce and predominantly retrospective, reporting inconsistent associations to new neurological deficits and prolonged hospital stay. Here we describe a protocol for a prospective observational study of hyperlactatemia during and after elective tumor craniotomy and the association with postoperative outcome, as well as selected pathophysiological aspects, and possible risk factors. We will include 450 brain tumor patients scheduled for elective craniotomy. Arterial blood samples for lactate and glucose measurement will be withdrawn hourly during surgery and until six hours postoperatively. To further explore the association of hyperlactatemia with perioperative insulin resistance, additional blood sampling measuring markers of insulin resistance will be done in 100 patients. Furthermore, in a subgroup of 20 patients, blood from a jugular bulb catheter will be drawn simultaneously with blood from the radial artery to measure the arterial to jugular venous concentration difference of lactate, in order to study the direction of cerebrovascular lactate flux. Functional clinical outcome will be determined by the modified Rankin Scale, length of stay and mortality at 30 days, 6 months, 1 year and 5 years. Clinical outcome will be compared between patients with and without hyperlactatemia. Multivariate logistic regression will be used to identify risk factors for hyperlactatemia. A statistical analysis plan will be publicized to support transparency and reproducibility. Results will be published in a peer-reviewed journal and presented at international conferences.

## Introduction

### Hyperlactatemia in brain tumor surgery: Clinical implications

Lactate metabolism in the human body is a complex, dynamic and incompletely understood process [1, 2]. In brain tumor surgery, hyperlactatemia occurs commonly with studies reporting prevalences of 32–68% [3–8]. Yet, it is unclear whether hyperlactatemia is an independent risk factor for patients undergoing tumor craniotomy. In an older randomized trial in patients with severe burns, a reduction in type 1 lactic acidosis with dichloroacetate neither worsened nor improved hemodynamics or survival [9], suggesting that lactate is not toxic in itself, but rather a marker of disturbed homeostasis. However, it has also been suggested that lactate in patients with intracranial tumors may act as a substrate for tumor cells and promote tumor growth, and that hyperlactatemia thus constitutes an independent risk factor for cancer patients [10, 11]. Existing studies of hyperlactatemia in neurosurgery have not reached a consensus on whether lactate accumulation is related to clinical outcome. Thus, some have reported an association with longer hospital stay [5–8], a single study found a correlation with new neurological deficits [6], while others found no association with outcome [3, 4]. Available studies in this field are predominantly retrospective [3–7] with only one existing prospective study, which was terminated early based on an interim analysis indicating futility [8].

### Hyperlactatemia in brain tumor surgery: Pathophysiological implications

The cause of hyperlactatemia in brain tumor surgery is debated. Both tumor characteristics [10, 12–14], comorbidity [15], perioperative rhabdomyolysis [16], length of surgery [7], and type of anesthesia [17] have been suggested to play a part.

Lactate is well-known as a marker of global or regional ischemia, but as an additional consideration hyperlactatemia is also a marker of increased non-oxidative glycolysis and may be induced by hyperglycemia in healthy subjects [18]. Insulin resistance is a common side effect of glucocorticoid treatment and can also be induced in healthy subjects after short-term treatment [19]. As the majority of patients undergoing tumor craniotomy are treated with glucocorticoids either preoperatively (especially prednisolone to reduce edema and thus intracranial pressure), intraoperatively (especially dexamethasone, to reduce the perioperative stress response) or both, glucocorticoid-associated insulin resistance is an attractive explanation of hyperlactatemia after tumor craniotomy.

Lactate has previously been shown to act as a substrate for the brain in conditions with hyperlactatemia such as physical activity or lactate infusion [20]. It is therefore likely that perioperative hyperlactatemia associated with tumor craniotomy is also associated with increased cerebral lactate metabolism and, therefore, a net cerebrovascular lactate influx (i.e., a positive arterial to jugular venous concentration difference). This has never been addressed and would contrast with the usual finding of a slight net cerebrovascular lactate outflux from the brain to the bloodstream (i.e., a negative arterial to jugular venous concentration difference) at normal serum lactate.

The present research protocol describes a prospective study consisting of four sub-studies to further explore hyperlactatemia in tumor craniotomy patients. We intend to investigate whether hyperlactatemia is related to clinical outcome (sub-study I) and identify possible risk factors associated with hyperlactatemia (sub-study II). In subsets of patients, we aim to study whether hyperlactatemia in this context is associated with pre- and postoperative insulin resistance (sub-study III) as well as a net cerebrovascular influx of lactate (sub-study IV). We hypothesize that tumor size, preoperative glucocorticoid dose and the severity of hyperlactatemia is associated to functional clinical outcome, with preoperative glucocorticoid dose as the independent risk factor. Furthermore, we expect the severity of insulin resistance and hyperglycemia to be associated with the severity of hyperlactatemia, and that hyperlactatemia is associated with a net cerebrovascular influx of lactate.

## Methods and analysis

### Study design

This single-center, prospective observational cohort study will be conducted at the Department of Neurosurgery and Neuroanaesthesiology, Rigshospitalet, Copenhagen, Denmark.

### Study population

The Department of Neurosurgery and Neuroanaesthesiology, Rigshospitalet, performs an average of 20 elective craniotomies per week, most of these procedures are carried out on patients with a brain tumor. This study will include 450 elective tumor craniotomy patients.

#### Inclusion criteria

Patients who meet the following criteria will be included in the study: (1) patients with a full mental capacity who are ≥ 18 years old and scheduled for elective brain tumor craniotomy; (2) patients understanding written and spoken Danish.

#### Exclusion criteria

Patients who meet any of the following criteria will be excluded from the study: (1) scheduled for stereotactic biopsy; (2) scheduled for pituitary surgery; (3) lack of ability to provide written informed consent; (4) previously enrolled and scheduled for reoperation.

### Consent to participate

Patients selected and booked for elective tumor craniotomy will be approached during their preoperative visit and assessed for study eligibility. Potential participants will be provided with verbal and written information by the investigator and given an opportunity to ask questions about the in a private atmosphere with the ability to have a bystander. Potential candidates are allowed time to consider their willingness to participate. All participation is voluntary and requires written consent that can be withdrawn at any time.

### Risks, side effects and disadvantages for study participants

All participants will receive standard clinical treatment, supplemented by additional blood sampling from pre-existing intravascular catheters and two standardized neurological disability assessments using modified Rankin Scale (mRS). In a subgroup of 20 patients, jugular bulb catheterization will be performed after induction of general anesthesia. This ultrasound-guided procedure is associated with a minor risk of bleeding but is otherwise risk-free [21]. There is no increased risk of infection during blood sampling, as blood is drawn under aseptic conditions. Participants are covered by the insurance of Rigshospitalet and the Danish Patient Compensation Association.

### Sample size calculation

The sample size calculation is based on the study by Brallier et al (6). This study observed an incidence of new neurological deficits in 15% of craniotomy patients with S-lactate > 2.2 mmol/L, compared with 7% in craniotomy patients with S-lactate ≤ 2.2 mmol/L. A standardized difference of 0.26 was calculated. Assuming a power of 0.8 and a level of significance of 0.05 and using a graphical approximation [22] a sample size of 450 patients for the primary endpoint was reached.

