### Study endpoints

#### Primary endpoints

Sub-study I: Change in mRS from preoperative assessment to 30 days after surgery, in patients with and without hyperlactatemia.

Sub-study II: Prevalence of hyperlactatemia (defined as at least one measurement of S-lactate> 2.2 mmol / L).

Sub-study III: Association between preoperative and/or intraoperative glucocorticoid treatment, HbA1c and pre-/ postoperative insulin resistance (measured by HOMA-IR), adjusted for hours after surgery.

Sub-study IV: Perioperative change in a-jD (lactate) corrected for change in a-jD (O_2_) from first to last measurement.

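### The 450 patients and 80% power attributed to the primary endpoint were derived from new neurological deficits, not from change in mRS

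*Protocol article*

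**What the plan says.** Under Sample size calculation, the article takes its inputs from one earlier study: "This study observed an incidence of new neurological deficits in 15% of craniotomy patients with S-lactate > 2.2 mmol/L". For patients at or below that threshold, the figure it gives is 7%. It continues: "A standardized difference of 0.26 was calculated". With power 0.8, significance level 0.05 and a graphical method, "a sample size of 450 patients for the primary endpoint was reached". It states neither the sidedness of the test nor the assumed split between the lactate groups.

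Under Primary endpoints, sub-study I has: "Change in mRS from preoperative assessment to 30 days after surgery, in patients with and without hyperlactatemia". The primary endpoints of the other three sub-studies are the prevalence of hyperlactatemia, an association with HOMA-IR, and the change in the lactate difference between arterial and jugular blood. None of them is new neurological deficits. Deficits recorded on admission and on discharge appear only under Exploratory endpoints.

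On group sizes, the Introduction reports that "hyperlactatemia occurs commonly with studies reporting prevalences of 32–68" per cent.

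**The concern.** A sample size calculation supports a power claim only for the outcome whose inputs it uses. Here the claim is attached to change in mRS, but the inputs describe something else. The two outcomes differ in instrument (a clinician's neurological examination versus an mRS rating), in timing (discharge versus day 30) and in scale (an incidence versus a change on an ordinal scale). The article gives no mRS difference, standard deviation or responder definition that would carry the 15% versus 7% over to the mRS.

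The calculation also treats the two groups as equal, although they are formed by observed lactate and the design does not control their sizes.

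The stake is how a null primary result would be read. The Introduction describes conflicting findings and one prospective study stopped for futility. The Discussion makes a possible randomized trial depend partly on whether hyperlactatemia appears to be an independent risk factor for functional outcome. A null mRS result would then be set against a power figure that was never derived for the mRS.

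**Working it through.** **Inputs from the article:** rates 0.15 and 0.07; standardized difference 0.26; power 0.80; alpha 0.05; N = 450 (Sample size calculation); hyperlactatemia prevalence 32–68% (Introduction). **Assumption:** a two-sided test, because sidedness is not stated. Then z = 1.96 + 0.8416 = 2.8016, and its square is 7.849.

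**1. The article's own figures.** The mean rate is 0.11, so d = 0.08 / √(0.11 × 0.89) = 0.2557. This rounds to the stated 0.26, which is therefore reproduced.

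For equal groups, total N = 4 × 7.849 / d²:
- d = 0.26: 31.396 / 0.0676 = 464 (466 when each group is rounded up to 233)
- d = 0.2557: 480

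The pooled two-proportion formula gives, per group, [1.96 × √(2 × 0.11 × 0.89) + 0.8416 × √(0.1275 + 0.0651)]² / 0.08² = (0.867 + 0.369)² / 0.0064 ≈ 239, or 478 in total.

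So 450 is not reproduced exactly, but it is close. Solving 31.396 / d² = 450 gives d = 0.264, a very small distance from 0.26 on a graph.

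**2. Power of 450 for 15% versus 7%.** With n₁ hyperlactatemic and n₂ normolactatemic patients and pooled rate p, power = Φ{[0.08 − 1.96 × √(p(1−p)(1/n₁ + 1/n₂))] / √(0.1275/n₁ + 0.0651/n₂)}. At 225/225 this is Φ[(0.08 − 1.96 × 0.02950) / 0.02926] = Φ(0.758) = 77.6%.

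| Hyperlactatemia | n₁ / n₂ | Normal approximation | Exact, uncorrected chi-square | N for 80% |
|---|---|---|---|---|
| 32% | 144 / 306 | 74.4% | 75.1% | 522 |
| 50% | 225 / 225 | 77.6% | 78.7% | 478 |
| 68% | 306 / 144 | 69.0% | 70.0% | 573 |

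The N column uses the pooled formula, and both rates are held fixed at every split. Under the normal approximation the best possible split gives 77.8%, so no split reaches 80%.

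**3. Sidedness.** A one-sided 5% test would give 80.3–85.9% over these splits. The article names no such test, and one-sided formulas give 378 patients (426 with continuity correction), further from 450 than the two-sided 464–478.

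**4. The primary endpoint.** Power for change in mRS cannot be computed, because the article gives no mRS difference or SD. What can be given is a detectable difference in SD units, if the change is compared as a mean: 2.8016 / √(450 f(1−f)), where f is the hyperlactatemic share.
- f = 0.50: 2.8016 / √112.5 = 0.264 SD
- f = 0.32 or 0.68: 2.8016 / √97.92 = 0.283 SD

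These are for 80% power, before missing data and covariate adjustment.

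**The case against.** The best defence concerns the arithmetic. The article discloses a graphical method. At its own d of 0.26, power with 450 in equal groups is 78.7%, and the N is about 3% below the formula value, which is plausible for a graph reading. This stands, so the equal-group shortfall is minor and should not be called a calculation error.

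The prevalence range spans several earlier studies whose thresholds and sampling windows the article does not give, and the 15% and 7% need not stay fixed as prevalence changes. This also stands as a caution: 69–70% belongs to the extreme upper end of the range.

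New deficits may have been meant as a proxy for worsening on the mRS, and a dichotomised mRS analysis is not excluded. That is possible, but the article does not say so, and as written it assigns the figure to the primary endpoint.

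A reader might infer that the study is underpowered for change in mRS. The article does not support that: without an mRS effect size, its power could lie above or below 80%. A reader might also infer that loss to follow-up was ignored. A condensed article may leave that allowance to the full protocol, so its absence here is no finding. Finally, the article plans to analyze lactate as a continuous variable too, so the outcome analysis does not rest on the two-group comparison alone.

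**Conclusion.** The concern holds, chiefly as a mismatch between endpoint and calculation. The 80% power is stated for the primary endpoint but derived from an outcome that is only exploratory in this study. This conclusion needs no assumption about sidedness or group split.

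The numerical shortfall is secondary. Assuming a two-sided 5% test and fixed rates of 15% and 7%, it is about 1–2 percentage points with equal groups. It grows to about 5–6 points at 32% hyperlactatemia and 10–11 points at 68%. It becomes material only through the article's own prevalence range. Nothing here shows that 450 is too few for the mRS analysis.

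**What to change.** Keep N = 450 and reword the Sample size calculation section:

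- Say that 450 was derived from the reported incidence of new neurological deficits, and remove the statement that it gives 80% power for the primary endpoint. If deficits were intended as a proxy for mRS change, say so and justify the link.
- State the sidedness and the assumed group split, and give power for 15% versus 7% as about 69–79% over prevalences of 32–68%.
- State what 450 can detect for change in mRS under the analysis actually planned. If the change is compared as a mean, this is 0.264 SD (50:50) to 0.283 SD (32:68 or 68:32) at 80% power, before missing data and adjustment. If the analysis is ordinal or dichotomised, the figure must be recomputed on that basis.
- Any allowance for missing mRS or for confounding should be labelled as an assumption and shown over a range.

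The cost is rewording and a less favourable power statement. No patients, visits or measurements are added.

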### Data collection specifications

This study will acquire data from the patient medical charts, perioperative monitoring, blood analyses, two neurological disability assessments and the Danish Cause of Death Register (Fig 1).

**Fig 1 pone.0271682.g001:**
[figure not shown]
Timeline for patient inclusion and data collection. Patients are assessed for study eligibility during their preoperative visit. Preoperative mRS is assessed upon study inclusion. Hourly blood gas test from arterial cannula (N = 450) and jugular vein (N = 20) throughout surgery, starting at skin incision, and continuing for 6 postoperative hours in the Post Anesthesia Recovery Unit. Additional analyses of insulin resistance measured perioperatively and before food intake, the day after surgery, in a subgroup of patients (N = 100). Continuous data collection from perioperative monitoring and patient journal until discharge from hospital. Follow-up mRS assessment 30 days after surgery. Mortality data are obtained from the Danish Cause of Death Register after 30 days, 6 months, 1 year and 5 years.

#### Preoperative data collection

The following demographic information is retrieved from patient file: age, sex, BMI, preoperative neurologic disability assessed by mRS, comorbidity, tumor characteristics (including tumor location and volume from preoperative MRI), medication (including any glucocorticoid expressed as cortisol equivalents) and biochemistry.

#### Intraoperative data collection

Data collection from patient monitors (invasive and non-invasive blood pressure, saturation, heartrate, and ECG), medication, transfusions and events or complications during anesthesia / surgery.

Blood is drawn from arterial cannula (the cannula is inserted into the radial artery by an anesthesiologist shortly after induction of anesthesia, as part of the standardized perioperative monitoring) and subjected to analysis as follows:

For all sub-studies, S-lactate, P-glucose, SaO_2_ and PaO_2_, using a point-of-care ABL800 FLEX blood gas analyzer (Radiometer) hourly from the time of skin incision to the end of surgery. (N = 450 patients)For sub-study III and IV, HbA1c, insulin, C-peptide, glucagon, and IL-6 immediately after induction and before treatment with intraoperative glucocorticoids. (N = 100 patients)For sub-study IV, ultrasound-guided retrograde catheterization (1-lumen, 16 G, 16 cm, Teleflex/Arrow) of the internal jugular vein is inserted shortly after induction of general anesthesia. Analysis of arterial and jugular bulb levels of S-lactate, P-glucose and PO_2_ are performed hourly as described above (N = 20 patients).

#### Data collection in Post Anesthesia Recovery Unit

Blood is drawn from arterial cannula immediately upon arrival to the Post Anesthesia Recovery Unit (before food intake) to analyze P-insulin, C-peptide, glucagon, and IL-6, after which patients are allowed food intake until 2 am (N = 100 patients). Hourly analysis of S-lactate, P-glucose, SO_2_ and PO_2_ is measured in blood from the arterial (N = 450 patients) and jugular bulb catheter (N = 20 patients). The arterial cannula and jugular bulb catheter are removed before discharge to the neurosurgical ward, typically after 6 hours observation. The presence and degree of nausea / vomiting as well as pain, assessed by numeric or visual rating scale 0–10, are noted in the patient file at every hour. Time to mobilization in the Post Anesthesia Recovery Unit is noted as well.

#### Data collection during follow-up

The morning after surgery, at 7.30 am (after fasting from 2.00 am) blood is drawn from a peripheral or central vein to analyze fasting P-glucose, P-insulin, C-peptide, glucagon, and IL-6 (N = 100 patients). Tumor type is classified by histopathological analysis of the intraoperative biopsy (classification level: glioma vs meningioma vs metastasis vs neurinoma vs cavernoma vs other). The discharge day and time is automatically recorded in the medical chart. The investigator estimates neurological disability using mRS at follow-up assessment or over telephone 30 days after surgery. Mortality after 30 days, 6 months, 1 and 5 years is obtained from the Danish Cause of Death Register.

### Data management

Patient information is collected and stored by the investigators in accordance with the General Data Protection Regulation with consent and supervision from the Danish Data Protection Agency.

Data are kept confidential in Research Electronic Data Capture, a password-protected software that stores data in case report forms with restricted and secured access. Case report forms are only accessible to investigators and coinvestigators. Exported files are stored on an encrypted personal computer with limited access.

### Definitions and calculations

Hyperlactatemia is defined as the measurement of at least one value of S-lactate > 2.2 mmol / L during the observation period starting at surgical incision and ending after 6-hours of observation in the Post Anesthesia Recovery Unit.

Peak lactate is defined as the highest value of S-lactate measured during the observation period.

Mean S-lactate is calculated as the area under the curve for S-lactate over time during the observation period, divided by the duration in hours. This is calculated to estimate the “total” lactate load regardless of whether the triggers occur pre-, intra- or postoperatively.

Intra- / postoperative lactate excess is calculated as mean S-lactate minus S-lactate at surgical incision. This is calculated to estimate the "pure" perioperative contribution to the lactate load.

Arterio-venous concentration difference (a-jD) for lactate, glucose, and oxygen: the concentration in jugular bulb blood minus the concentration in arterial blood.

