#### Secondary endpoints

Sub-study I:

Length of hospital stay, from day of surgery to discharge, in days.Mortality at 30 days, 6 months, 1 year and 5 years (6 months, 1 year and 5 years mortality will not be included in the initial data analysis and publication).

Sub-study II:

Association between pre- / intraoperative risk factors (specified in exploratory endpoints) and hyperlactatemia.

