#### Exploratory endpoints

Tumor type, location and estimated volume on preoperative MRI scan.BMI and comorbidity (Charlson Comorbidity Index), with focus on insulin dependent or non-dependent diabetes mellitus type 1 or 2 and liver / kidney disease.Neurological deficits at admission and at discharge. The deficits are assessed by the admitting and discharging clinician through standard neurological examination (mental status, cranial nerves, motor system, reflexes, sensation, and cerebellar function).Preoperative chemotherapy, radiation, or immunotherapy.Dose and duration of pre-, intra-, and post-operative treatment with glucocorticoids (expressed as cortisol equivalents in mg).Surgery duration (minutes) and surgery events (such as other procedures during the surgery and complications, using Landriel Ibañez classification).Position during surgeryComplete or incomplete total resection of tumor, as indicated by the neurosurgeon in the operative report.Type of anesthesia: total intravenous anesthesia, inhalation anesthesia, awake craniotomy.Intra- and post-operative hypotension (defined as MAP < 60 for > 15 min or MAP < 30% of preoperative resting MAP for > 15 min) and treatment with vasopressors (ephedrine, noradrenaline, methoxyarene) in mg for total surgery duration.Perioperative fluid therapy volume and type, as well as total urine output in mL / hour during surgery and in the Post Anesthesia Recovery Unit.Estimated blood loss and blood transfusion volume.Perioperative blood gas parameters: pH, glucose, PaO_2_, PaCO_2_, Base Excess, Hb, HCO_3_, Na, K, Cl.Postoperative nausea, vomiting and pain. Pain assessed by numeric or visual rating scale 0–10.Mobilization time to upright sitting position in the Post Anesthesia Recovery Unit, measured in hours.

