## Discussion

Even though hyperlactatemia is common in tumor craniotomy patients, little is known of the underlying pathophysiology and the clinical effect of this phenomenon. The results of this study will provide new knowledge about the incidence and possible risk factors for hyperlactatemia in patients undergoing tumor craniotomy, as well as the potential association with functional outcome. It will also explore the role of the surgical stress response and glucocorticoid-associated insulin resistance for the development of hyperlactatemia and provide an indication of the pathophysiological significance for the brain by measuring the net cerebrovascular flux of lactate.

Previous studies on this subject [3–7] have been retrospective and may therefore have been susceptible to selection bias. With a prospective study we hope to avoid such bias by sampling data according to a prespecified protocol. There are, however, possible contributing factors to hyperlactatemia that we have not accounted for in our design. Thus, perioperative rhabdomyolysis may increase S-lactate [23]. In neurosurgery, rhabdomyolysis has been reported amongst patients who are placed in the lateral position, and for those who undergo surgery lasting more than 5 hours [16]. Myoglobin, creatine kinase, lactate dehydrogenase and creatinine are measured in our department only if there is clinical suspicion of rhabdomyolysis or kidney failure. We would most likely detect severe rhabdomyolysis, as we routinely monitor patient mobility, urine output and electrolyte levels. As part of our study design, we record perioperative positioning, duration of surgery, and BMI as possible contributing risk factors for hyperlactatemia.

Additionally, the type and volume of intravenous fluid administration may decrease or increase lactate levels by dilution or exogenous contribution, respectively. The intravenous fluid of choice in our department is isotonic saline; selected patients may receive hypertonic saline or Ringer lactate on specific indications. We do not use mannitol. Intravenous fluid type and volume in each perioperative phase will be reported in the final manuscript.

Another limitation of our study is the time period for lactate measurements. Due to the organization of perioperative care, we cannot measure S-lactate for longer that 6 hours postoperatively and therefore cannot differentiate between patients with late, prolonged, or short-lived hyperlactatemia.

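### The any-value definition of hyperlactatemia gives longer operations more chances to be positive, which biases the surgery-duration odds ratio in sub-study II upward by an amount the protocol does not allow one to fix

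*Protocol article*

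**What the plan says.** The Definitions and calculations section of the protocol article makes a patient hyperlactatemic on "the measurement of at least one value of S-lactate > 2.2 mmol / L during the observation period starting at surgical incision". The same sentence closes the window some hours after the operation, with the words "ending after 6-hours of observation in the Post Anesthesia Recovery Unit". Under Intraoperative data collection, arterial lactate is measured "hourly from the time of skin incision to the end of surgery". For the recovery unit the text is "Hourly analysis of S-lactate, P-glucose, SO_2_ and PO_2_ is measured in blood from the arterial (N = 450 patients", and the cannula is typically removed after about six hours. So the recovery part is roughly the same for all patients, and the intraoperative part is as long as the operation.

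Duration is also an explanatory variable. The secondary endpoint of sub-study II is "Association between pre- / intraoperative risk factors (specified in exploratory endpoints) and hyperlactatemia", and the list it points to contains "Surgery duration (minutes) and surgery events". The Introduction notes that "length of surgery [7], and type of anesthesia [17] have been suggested to play a part", and the Discussion says "we record perioperative positioning, duration of surgery, and BMI as possible contributing risk factors for hyperlactatemia". The Abstract names multivariate logistic regression for this analysis.

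The Definitions section also gives a mean S-lactate, the area under the curve divided by hours. The Statistical analysis section speaks of continuous lactate for the outcome analysis and does not say that it will be used for risk factors. The Discussion names the six-hour postoperative limit as a weakness, but not the unequal length of the window before it.

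**The concern.** The binary variable asks whether the maximum of a patient's hourly values exceeds a fixed cut. Adding values can only raise that maximum or leave it unchanged, so the probability of being positive rises with the number of samples. That number is set by surgery duration. In sub-study II the dependent variable is thus tied by construction to one of the covariates tested against it.

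At stake is how a positive duration coefficient is read. It could mean that long surgery raises lactate, or only that long surgery is observed for longer. Putting duration in the model may limit the leak into covariates that travel with it, such as blood loss or fluid volume, but cannot separate the two explanations for duration itself. This arises in fully sampled patients and does not depend on anyone leaving the recovery unit early.

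**Working it through.** The protocol gives no figure on this point to reproduce. From it come the cut-off rule, the hourly schedule, N = 450 and the cited prevalence range of 32–68% (Introduction). The within-patient correlation and the distribution of surgery duration are not given, so they are assumed and varied.

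**Number of samples.** With surgery of h whole hours, k = (h + 1) + 6. For 2 h, k = 9; for 6 h, k = 13; for 8 h, k = 15.

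**Model A: correlated hourly values, no effect of duration.** Values are normal with common within-patient correlation ρ. The probability of at least one value above the cut c is the average over x ~ N(0,1) of 1 − Φ((c − √ρ·x)/√(1 − ρ))^k. The cut is set so that prevalence at 4 h of surgery (k = 11) is 50%.

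| ρ | 2 h | 6 h | 8 h | OR, 6 h vs 2 h |
|---|---|---|---|---|
| 0 | 43.3% | 55.9% | 61.1% | 1.66 |
| 0.5 | 46.5% | 52.8% | 55.2% | 1.29 |
| 0.8 | 48.1% | 51.6% | 52.9% | 1.15 |
| 0.9 | 48.7% | 51.1% | 52.0% | 1.10 |
| 0.95 | 49.1% | 50.7% | 51.2% | 1.06 |

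With prevalence set to 32% or 68%, the whole range for 6 h against 2 h is 1.06 to 1.85. For 8 h against 2 h at 50% prevalence the ratios are larger: (0.611/0.389)/(0.433/0.567) = 2.06 at ρ = 0, and (0.529/0.471)/(0.481/0.519) = 1.21 at ρ = 0.8.

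**Model B: stable patient levels.** Patient level is log-normal (median 1.6 or 1.8 mmol/L, log-SD 0.4), hour-to-hour CV is 5–15%, and autocorrelation is 0 or 0.5. From 2 h to 8 h of surgery, prevalence rises by about 1–4 percentage points, an OR of 1.05–1.18.

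**Model C: independent short excursions.** With probability p per hourly sample, P = 1 − (1 − p)^k.
- p = 0.03: 1 − 0.97^9 = 24.0%; 1 − 0.97^15 = 36.7%; OR = (0.367/0.633)/(0.240/0.760) ≈ 1.8.
- p = 0.05: 1 − 0.95^9 = 37.0%; 1 − 0.95^15 = 53.7%; OR = (0.537/0.463)/(0.370/0.630) ≈ 2.0.

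**How often duration would reach P < 0.05 under the null.** Simulation with N = 450 and 1,000 runs per setting. Duration is log-normal (median 3.5 h, log-SD 0.4, limited to 1–9 h) and has no effect on lactate. Prevalence is 50%, with a logistic regression on duration alone.

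| Patient share of variance | Serial correlation | OR per hour | Significant |
|---|---|---|---|
| 0 | 0 | 1.14 | 55% |
| 0.5 | 0 | 1.07 | 20% |
| 0.5 | 0.5 | 1.08 | 19% |
| 0.8 | 0.5 | 1.05 | 9% |
| 0.8 | 0.8 | 1.04 | 10% |
| 0.9 | 0.8 | 1.02 | 5.5% |

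The Monte Carlo standard error at 5% is √(0.05 × 0.95/1000) = 0.7 points, so the last row cannot be told from the nominal level. In the same runs, classifying everyone on seven values gave 3.6–5.3%, and linear regression of mean S-lactate on duration gave 3.5–5.6%. The seven values were each patient's first seven. Repeating the check with the incision value plus six recovery values also stayed close to nominal.

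**The case against.** Four objections deserve weight.

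1. *It is an estimand choice.* At least one exceedance is a cumulative occurrence over the perioperative period, and a patient operated on for longer really does have more time in which to exceed 2.2. That is fair for prevalence, and it is why the definition need not be replaced. It does not help sub-study II, where the coefficient is meant to say something about duration as a contributor to lactate.

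2. *The size may be trivial.* This stands in part. The odds ratios of 1.8–2.0 treat every hour as an independent event, and 8 h against 2 h is a wide assumed contrast. If lactate moves slowly, the null odds ratio is near 1.1 and the error rate is barely raised. The Discussion allows for late, prolonged or short-lived hyperlactatemia, so the protocol settles neither case.

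3. *Sub-study I is already covered.* Largely true. The outcome analysis is to use continuous as well as binary lactate, and the mean is already divided by hours. A reader might infer that the comparison of mRS and stay is invalidated. The documents do not support that: the groups do carry the dependence on duration, but any resulting bias is unquantified and a check is planned.

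4. *Adjustment and sensitivity analyses belong in the SAP.* Agreed, and their absence here is not the criticism. The definition and the risk-factor list, however, are fixed in the protocol article itself.

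**Conclusion.** The point holds as an upward bias of certain direction and uncertain size in the association between surgery duration and hyperlactatemia in sub-study II, a secondary endpoint. If duration has no effect on the lactate level at any time point, the odds ratio for long against short surgery is still about 1.05–1.2 when hourly values track closely. It is about 1.7–2.0 when excursions are short-lived and near-independent, and somewhat higher at the top of the cited prevalence range. These figures rest on assumed correlations and durations.

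Two stronger readings go too far. One is that duration will emerge as a risk factor whatever the truth: under the null it was significant in anything from about 5.5% to 55% of simulated studies, so it is biased towards appearing as one and no more. The other is that sub-study II can never separate a true effect from longer sampling: the hourly values are collected, so an analysis on a common set of samples can address this without any design change.

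**What to change.** Keep any value above 2.2 mmol/L as the main definition and as the descriptive prevalence, so that it stays comparable with earlier studies.

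For the surgery-duration association in sub-study II, add an analysis that classifies each patient on a common set of samples: the incision value plus the same number of hourly recovery-unit samples, chosen so that every patient has them. State that number before the association is examined. It should not rest on a recovery-arrival lactate, because the explicit arrival draw is for insulin-related markers and IL-6 in 100 patients. Nor should it assume six recovery values in everyone, because the six-hour stay is only typical.

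Mean S-lactate can be a second check, with the note that it is neutral to duration only if intraoperative and recovery levels are similar. Otherwise a longer operation shifts the mean through the weighting of the two phases. Peak lactate is no substitute, as it has the same dependence on the number of samples.

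In sub-study I no new analysis is needed, provided the continuous measure used is the one divided by hours and not the raw area, which itself grows with duration.

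The cost is one more derived variable from data already collected. The downside is that mid-operation peaks are ignored in that analysis.
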